### Trial status

This study, protocol version V.1, dated 24 May 2019, commenced recruitment in March 2019. This pilot study will be performed over a 6-month period. We will disseminate trial results through research articles.

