### Study design

This pilot study is a randomized controlled trial of two parallel groups. The intention of this study is to evaluate the feasibility and acceptability of IPT in a online format for a sample of prenatal women. Additionally, this study is a parallel group, Consolidated Standards of Reporting Trials revised 2010 compliant, pilot randomized controlled trial of e-IPT versus routine prenatal care (Fig. 2). Data collection points are at baseline, 3 months postrandomization, and at 3 and 6 months postpartum. The current trial protocol has been approved by the Conjoint Health Research Ethics Board at the University of Calgary (REB16–0061). This study is registered with ClinicalTrials.gov (identifier NCT1901796).

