### Inclusion and exclusion criteria

Eligible participants are women who reside in Alberta, Canada, are over the age of 18 years and are pregnant, from conception to 30 weeks gestation. Participants must be able to read and write in English. Participants must be capable of providing informed consent and of learning and understanding new information such as contained in the e-IPT modules. Additionally, participants must have access to online hardware including a digital device (either a computer, smart phone, or tablet).

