### Both groups

All applicants will complete the Depression, Anxiety, and Stress Scale-21 (DASS21) and the Edinburgh Postnatal Depression Scale (EPDS) on recruitment (prerandomization) to provide baseline data on their mental health status. All participants (control and intervention groups) assessed as having thoughts of self-harm will receive a computerized message offering then crisis line/emergency room contact information and informing them that they will be contacted by the study nurse. Following randomization, participants will complete the baseline series of questionnaires which comprehensively assess a variety of demographics and psychosocial constructs (T_1_) (Fig. 1). These questionnaires will be completed again at 3 months postrandomization (T_2_), after 8 months of pregnancy (T_3_), and 3 months postpartum (T_4_).

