#### Strategies for assessing adherence and attrition

To assess adherence, the completion of online questionnaires and the intervention homework will be recorded through a specific application through Google Analytics. This application will include the length of time taken to complete modules and the number of modules completed. To assess attrition, comparisons between the attrition rates of the control and the intervention groups will be performed.

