### Data analyses

#### Feasibility and acceptability of the intervention

Feasibility and acceptability, in addition to the qualitative data obtained from the interviews, will be characterized using descriptive statistics (frequencies, proportions, means, standard deviations). Feasibility will be assessed as the rate of retention in the study and percentage of modules completed. The acceptability of this intervention will consist of an analysis of the perceptions of the prenatal women regarding the intervention and its various features. Acceptability will be assessed by open-ended questions exploring the reported ease for women in navigating the online intervention. Participants will also be asked about what was useful and that was difficult in navigating this online intervention. The qualitative data will be analyzed using inductive thematic analysis. This method was chosen because it allows patterns and key themes within the data to be identified [76]. The three-stage process of thematic analysis will involve: 1) generating code; 2) merging and renaming similar codes; and 3) grouping codes into overarching themes that best describe the data [77].

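### A 6-month pilot cannot follow most of its sample to the last scheduled visit, so retention over the full schedule would go unobserved for most women

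*Protocol article*

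**What the plan says.** All references are to the protocol article.

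- **Duration.** Trial status says that the study "commenced recruitment in March 2019" and that "This pilot study will be performed over a 6-month period".
- **Entry window.** Inclusion and exclusion criteria admits women who "are pregnant, from conception to 30 weeks gestation".
- **Last visit.** Both groups lists the later questionnaires as "after 8 months of pregnancy (T_3_), and 3 months postpartum (T_4"); the abstract and Data collection agree. Study design differs: "Data collection points are at baseline, 3 months postrandomization, and at 3 and 6 months postpartum". The intervention section also gives 3 and 6 months postpartum.
- **Use of retention.** Primary outcomes makes enrolment and retention part of feasibility. The analysis section says "Feasibility will be assessed as the rate of retention in the study and percentage of modules completed". For attrition, "comparisons between the attrition rates of the control and the intervention groups will be performed".
- **Interviews.** Screening, consent, and enrollment places the telephone interview after the 3-month postpartum questionnaire. Data Availability expects the feasibility and acceptability interviews to be finished by October 2019.
- **Missing data.** Quantitative analysis says only that missing values will be handled by multiple imputation.

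**The concern.** A woman who joins in mid-pregnancy must finish the pregnancy and then wait three more months before her last questionnaire is due. For most permitted entry times that takes longer than the stated length of the whole study.

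Two things are at stake. First, retention is a primary feasibility measure, and the pilot is meant to inform the full trial, whose sample size section assumes 25% attrition plus 5% loss to follow-up. A pilot that stops before most final visits are due cannot check those rates over the full schedule. Second, the final-visit outcomes in the repeated-measures analysis would be missing for most women simply because follow-up ended. The few observed would be a selected group: late in pregnancy at entry and early in the calendar.

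**Working it through.** **Inputs from the protocol:** study length 6 months = 26.09 weeks; entry up to 30 weeks' gestation; T4 at 3 months (13.04 weeks) postpartum, or a last visit at 6 months (26.09 weeks) postpartum; N = 160, 80 per arm.

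**Assumptions (not in the protocol):** birth at 40 weeks, range 37–41; gestation at entry uniform from a lower bound of 4, 8, 12 or 20 weeks up to 30; accrual uniform over its duration; no dropout.

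**1. Time from entry to T4.** For entry at g weeks: (40 − g) + 13.04.

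- g = 30: 23.0 weeks (20.0 for birth at 37 weeks, 24.0 for birth at 41)
- g = 20: 33.0 weeks
- g = 12: 41.0 weeks
- g = 4: 49.0 weeks

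**2. Who fits inside the study.** A woman entering s weeks after the start needs s + 53.04 − g ≤ 26.09, so s ≤ g − 26.96. At g = 30 she must enter by week 3.04. At g = 27 she must enter essentially on day one. Below that, T4 is out of reach.

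**3. Share reaching T4 by 6 months.**

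| Accrual time | Share reaching T4 | Women of 160 |
|---|---|---|
| All on day one | 12–31% | 19–49 |
| 1 month | 4–11% | 7–17 |
| 3 months | 1–4% | 2–6 |
| 6 months | 1–2% | 1–3 |

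The ranges run from the 4-week to the 20-week lower bound on gestation at entry. Hand check at the 4-week bound:

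- Day one: 3.04/26 = 11.7%, × 160 ≈ 19.
- 6-month accrual: (3.04²/2)/(26.09 × 26) = 4.62/678.3 = 0.7%, × 160 ≈ 1.

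**4. The 6-month postpartum schedule.** The shortest time is (40 − 30) + 26.09 = 36.1 weeks. With birth at 37 weeks it is 33.1. Both exceed 26.09, so no one reaches that visit.

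**5. Reading the 6 months as recruitment only.** Twenty-three weeks before 31 October 2019 is 23 May 2019. A woman entering after that, even at 30 weeks' gestation, cannot complete the 3-month postpartum questionnaire by the end of October (mid-June if birth is at 37 weeks). The last women recruited would reach T4 in about February 2020 or later. With accrual spread over 6 months from 1 March, 10–26% of women (16–41 of 160) reach T4 by the end of October. That is about 8–20 in the intervention arm, against 30 interviews in Data collection and 15–30 in the abstract.

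**6. Earlier visits.** T2 is observable within 6 months for everyone if accrual takes 3 months or less, and for about half if it takes 6. Taking T3 as about 35 weeks' gestation (assumption) and entry uniform over 4–30 weeks, T3 is reached by (21²/2)/(26 × 26) = 33% with 6-month accrual and by 21/26 = 81% with day-one entry.

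**The case against.** The strongest reply is that the sentence stands next to the start of recruitment, so it may describe the recruitment period. The October 2019 date, 7–8 months after March, also suggests that data collection was expected to run past month 6. Both points have force. If follow-up ran to the end of October, T4 would be reached by 10–26% with 6-month accrual, 20–52% with 3-month accrual, and by a majority only if accrual were quick and entry mostly late in pregnancy. So the calculated shares do depend on a stop at 6 months. Neither reading makes the document consistent, however: as total duration the 6 months clashes with the visit schedule, and as recruitment time it clashes with the interview date, unless only the earliest completers are interviewed.

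A reader might also infer stronger claims that the text does not support:

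- **That T4 retention cannot be observed at all.** Since 23 weeks is less than 26, a small group can reach T4.
- **That the protocol defines retention as retention to T4.** It names no time point. T4 is simply the last visit on one of its two schedules.
- **That women cut off by the calendar will be counted or imputed as dropouts.** The protocol gives no such rule. It has only a general imputation statement, and an analysis plan that is not shown may deal with visits not yet due.
- **That retention can be estimated only to T2.** Step 6 shows that a sizeable share can reach T3.

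**Conclusion.** The point holds as an internal inconsistency that touches a primary measure. No analysis plan can supply visits that never fell due. If 6 months is the whole study, then retention over the full schedule, and the between-arm attrition comparison over that schedule, are unobservable for most of the sample: at least about two thirds of women under every entry pattern tried, and about 98–99% if accrual takes the full 6 months. On the 6-month postpartum schedule they are unobservable for everyone.

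The figures rest on birth at 40 weeks, uniform gestation at entry, uniform accrual and a stop at 6 months. The minimum of about 23 weeks to T4 (20–24 across the birth range) needs only the entry limit and the timing of birth. This should be corrected, but it does not undermine the design.

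**What to change.** Reconcile Trial status, the entry window, the two postpartum schedules (abstract, Both groups and Data collection against Study design and the intervention section), and the interview timing in Screening, consent, and enrollment and Data Availability.

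- **Preferred:** state 6 months as the recruitment period, keep the automated online questionnaires open until the last woman's final visit is due, and move the interview completion date to match.
- **If 6 months is fixed for the whole study:** name an earlier visit as the retention time point.
- **In either case:** compute retention and arm-specific attrition at each visit only among women whose visit has fallen due, and report visits never due separately, so that administrative cut-off is not read as dropout.

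The cost is wording plus one of two things. Extending follow-up means about 11 months of automated online follow-up after the last entry if she joins at 4 weeks' gestation and T4 is the last visit (49 weeks), or about 14 months on the 6-month postpartum schedule (49.0 + 13.04 = 62.1 weeks, allowing for rounding), with later completion. Fixing 6 months means a shorter retention horizon, which leaves postpartum retention untested before the full trial.

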## Data Availability

Participants will complete questionnaires online and these data will be sent to a secure Canadian Amazon server. There the data will be anonymized and then downloaded to a secure server at the Health Research Data Repository (HRDR), housed in the Faculty of Nursing, University of Alberta. Additionally, the data will be stored and analyzed within the HRDR. HRDR access is restricted to the research team conducting data analyses. Qualitative interviews will be digitally recorded and transcribed verbatim. These transcribed interviews and digital files will be password protected and stored on a password-protected computer in a locked, secure office at the University of Calgary. We expect to complete feasibility and acceptability interviews by October 2019.

## Abbreviations

CBT: Cognitive behavioral therapy
DASS21: Depression, Anxiety, and Stress Scale-21
e-IPT: Online interpersonal psychotherapy
EPDS: Edinburgh Postnatal Depression Scale
IPT: Interpersonal psychotherapy
